## Abstract

**Background:**

Transurethral resection of the prostate (TURP) has been the standard operation for benign prostatic obstruction (BPO) for 40 years, with approximately 25,000 procedures performed annually, and has remained largely unchanged. It is generally a successful operation, but has well-documented risks for the patient. Thulium laser transurethral vaporesection of the prostate (ThuVARP) vaporises and resects the prostate using a surgical technique similar to TURP. The small amount of study data currently available suggests that ThuVARP may have certain advantages over TURP, including reduced blood loss and shorter hospital stay, earlier return to normal activities, and shorter duration of catheterisation.

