### Rationale for the trial

The general population has an increased life expectancy, resulting in an ageing population. As BPO is a disease of older men, the number of patients with the condition is expected to grow by almost 50% by the year 2025, increasing the need for BPO surgery [2]. Furthermore, as the operation is increasingly conducted on older men (42% of the TURP operations in 2014–2015 were on patients older than 75 years), the risks of surgery associated with TURP will continue to increase. There is therefore sustained interest in the condition and increasing need to find safer techniques than TURP. The potential advantages of reduced blood loss, shorter hospital stay and earlier return to normal activities make laser vaporesection techniques attractive to both patients and health care providers. ThuVARP would allow urologists to operate on a wider range of men, including potentially those who are more frail and older, but with less risk. However, there is uncertainty about the degree of symptom improvement and improvement in quality of life in the short and longer term, which this trial addresses. Now is the ideal time to conduct the trial as the procedure has not yet been widely taken up across the UK.

An additional reason for early evaluation of ThuVARP is the promise it offers to convert BPO surgery from an inpatient operation into a day-case procedure. Shortened stay is increasingly important for the NHS both because of the increasing cost of inpatient beds, shortage of inpatient beds due to an ageing and increasingly co-morbid population, and the risk longer hospital stays present for such patients, for example of hospital-acquired infections.

In summary, although there is little existing work on ThuVARP, promising initial evidence from one RCT suggests that ThuVARP has equivalent clinical effectiveness when compared to TURP, albeit in a single Chinese centre. Our randomised study is designed to provide the high-quality evidence, in an NHS setting with a range of patient-reported, clinical and cost-effectiveness outcomes, which will underpin and inform future NICE guidance.

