#### Economic data collection

Details of initial hospital stay resource use, e.g. operation duration; operating staff; consumables; the time spent in recovery; length of stay on different wards; overall length of stay and treatment for complications, were collected on study-designed case report forms (CRFs) by the research nurse at the time of the inpatient/day-case stay for the initial surgery. Hospital patient-linked information costing systems are used if available to capture follow-up hospital use at the treating hospital. If this information cannot be accessed then subsequent inpatient stays, outpatient visits and procedures occurring at the treating hospitals are abstracted from the patients’ medical records and recorded on a CRF.

On discharge from hospital, and at 3 months follow-up the patients are given a study designed Resource Use Log (RUL) to be used as an aide memoire in which to record NHS and private community-based health care use, other NHS hospital health care use, medications, personal social service (PSS) resource use in addition to travel, time off work/usual activities and any other expenses resulting from their treatment [11]. These logs reflect the design of the 3-month and 12-month UNBLOCS Resource Use questionnaire. At 3 months and 12 months follow-up, participants are able to use the information from the RUL in order to complete the UNBLOCS Resource Use Questionnaire, which they take home from clinic, or receive by post along with a pre-paid return envelope. The EQ-5D-5L will be used to calculate quality-adjusted life years (QALYs). The new five-level EQ-5D is used in preference to the three-level one, owing to its improved discriminatory power [12].

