### Randomisation

All men who entered the trial were logged with the central study office and given a unique, six-digit study (participant) identification number.

Participants were randomly allocated to treatment arms using an automated web/telephone randomisation system provided by the Bristol Randomised Trials Collaboration (BRTC). This took place in the anaesthetic room when the patient was anaesthetised.

Randomisation was stratified by centre and whether the patient was eligible due to bothersome LUTS or urinary retention, and random blocking was employed (of two, four and six randomly allocated).

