Analyses of secondary analyses will employ linear, logistic or multinomial regression models as appropriate. Repeated measure models will explore any treatment-time interactions considering the 6 weeks and 3 months data in addition to baseline and 12 months. Potential effect modifiers, selected a priori and informed by previous evidence, will be explored using formal tests or interaction. These will include:Clinical diagnosis at baseline of LUTS secondary to BPO or urinary retention (stratification variable)Pre-operative prostate size measured by digital rectal examinationAgePatient co-morbidities at baseline (Charlson Comorbidity Index)Conduct of TURP procedures; whether monopolar or bipolar TURPLength of stay of procedures; including whether day-case or inpatient

Interpretation will focus on the confidence intervals only and will be hypothesis-generating since the trial is not powered for such analyses. No interim analyses are planned.

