## Discussion

This article describes a multicentre randomised trial to compare ThuVARP to the current gold standard TURP surgery for benign prostatic obstruction. The aim is to determine the relative clinical and cost effectiveness of the two alternative procedures, within the NHS.

The most significant challenge for the trial, during the recruitment phase, has been the capacity of participating Trusts to undertake the required surgery. Randomisation occurs in the operating theatre whilst the patient is under anaesthetic. Operating theatre availability and hospital bed pressures within Trusts, particularly during the winter months, slowed recruitment for this elective procedure, despite a ready pool of willing participants. Protected research operating time secured at two participating Trusts, the advent of day case procedures and multiple surgeons at sites, helped to overcome these challenges, albeit with additional time for recruitment required. It should be noted that the very difficulties experienced in conducting this trial, with the shortage of hospital beds impacting on the capacity for Trusts to operate, are the very same issues which ThuVARP has the promise to address, with its potential for shorter hospital stays, and shift to day case procedures.

This randomised study will provide the high-quality evidence, in an NHS setting with a range of patient-reported, clinical and cost-effectiveness outcomes, which will underpin and inform future NICE guidance in a timely manner.

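### Realised length of stay (day-case or inpatient) is listed as an effect modifier, although it is a post-randomisation outcome that ThuVARP is expected to change

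*Protocol article*

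**What the plan says.** The Statistical analysis section states: "Potential effect modifiers, selected a priori and informed by previous evidence, will be explored using formal tests or interaction". The list that follows gives clinical diagnosis at baseline, pre-operative prostate size, age, baseline co-morbidity, the type of TURP and, last, length of stay, "including whether day-case or inpatient". It closes with a limit on use: "Interpretation will focus on the confidence intervals only and will be hypothesis-generating since the trial is not powered for such analyses".

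Four other places bear on the last item.

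- **Randomisation:** "This took place in the anaesthetic room when the patient was anaesthetised".
- **Economic data collection:** length of stay is recorded on case report forms "at the time of the inpatient/day-case stay for the initial surgery".
- **Outcome measures:** length of hospital stay is a key secondary outcome.
- **Expected effect of ThuVARP on stay:** the Abstract mentions "reduced blood loss and shorter hospital stay", the Rationale gives as a reason for early evaluation "the promise it offers to convert BPO surgery from an inpatient operation into a day-case procedure", and the Discussion describes ThuVARP "with its potential for shorter hospital stays, and shift to day case procedures".

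**The concern.** A subgroup factor keeps the protection of randomisation only if allocation cannot influence it. The patient factors on the list meet that standard, since they are fixed at or before baseline. Realised stay does not: it comes into being after allocation, and the protocol expects the two operations to change it in different degrees.

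If stay also shares causes with 12-month symptoms (frailty, co-morbidity, complications), then sorting men by stay sorts them by prognosis, and does so differently in each arm. Suppose few TURP patients but many ThuVARP patients go home the same day. The TURP day cases are then the more selected, fitter group. The TURP inpatients are also fitter on average than the ThuVARP inpatients, because they include men who would have been day cases after laser. Two operations with identical effects could then appear to differ within both groups.

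The stake is interpretive. Conversion to day-case surgery is one of the stated reasons for the trial, and the trial is meant to inform national guidance, so a result split by day-case status is likely to be read closely.

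**Working it through.** **1. Order of events.** Allocation happens under anaesthetic, before surgery; stay is known only afterwards. Nothing in the article defines the modifier as a planned pathway, and the words length of stay describe something realised.

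**2. Size of the within-group bias.** The plan gives no figure to reproduce, so this is an illustration.

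- From the protocol (Sample size): IPSS SD 5; 163 completers per arm.
- Assumed: an unmeasured frailty factor with correlation *a* = 0.3 to 0.5 with 12-month IPSS and *b* = 0.5 to 0.7 with a normal latent stay; day-case rates *p* of 40 to 50% (ThuVARP) and 5 to 20% (TURP).
- Truth: no treatment effect on IPSS and no interaction.

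A man is a day case if his latent stay falls below a threshold set by his arm. With z the normal quantile of *p* and φ the normal density, the mean IPSS relative to the whole arm is

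- day cases: −5·a·b·φ(z)/p
- inpatients: +5·a·b·φ(z)/(1−p)

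These average to zero over the arm, so the overall arm comparison stays unbiased.

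Middle example, a = 0.3, b = 0.7, so 5ab = 1.05; rates 40% and 10%, with φ = 0.3863 and 0.1755:

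- day case: ThuVARP −1.05 × 0.3863/0.4 = −1.01; TURP −1.05 × 0.1755/0.1 = −1.84; difference +0.83
- inpatient: ThuVARP 1.05 × 0.3863/0.6 = 0.68; TURP 1.05 × 0.1755/0.9 = 0.20; difference +0.47 (from unrounded values)

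| Scenario (a / b; ThuVARP vs TURP day-case rate) | Day case | Inpatient | Interaction |
|---|---|---|---|
| 0.3 / 0.5; 40% vs 20% | +0.33 | +0.22 | 0.1 |
| 0.3 / 0.7; 40% vs 10% | +0.83 | +0.47 | 0.4 |
| 0.5 / 0.7; 50% vs 5% | +2.21 | +1.21 | 1.0 |

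Differences are ThuVARP minus TURP in IPSS units; positive means worse symptoms after ThuVARP.

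**3. The interaction test at trial size, same selection process in both arms.** Simulating the model IPSS ~ arm + day case + arm × day case with 163 per arm, the interaction has a standard error of about 1.5 units in the middle row and about 2.0 in the last. False positives at a nominal 5% are about 5% in the middle row and 7 to 8% in the last.

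**4. The interaction test when selection differs by arm.** Here TURP day-case status is driven by frailty and ThuVARP day-case status is almost unrelated to it, with rates of 26% (TURP) and 42% (ThuVARP). For a frailty–IPSS correlation of 0.3 to 0.5, the spurious differences are about +1.3 to +2.2 in day cases and −0.4 to −0.7 in inpatients. The spurious interaction is about 1.7 to 2.9 units, with false positives of 29% to 69%.

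**5. Control.** If day-case status does not depend on allocation, as with a variable fixed beforehand, the interaction is about 0 and false positives are 4.7% to 5.1%.

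**The case against.** The strongest reply is that the protocol plans interaction tests, and that under a common selection process those tests keep close to their nominal error rate. That stands: steps 2 and 3 show much more bias in the within-group contrasts than in the interaction. A reader might infer that the interaction test is certainly biased, or that ThuVARP would necessarily look worse in both groups. The documents support neither. Size and sign depend on how men come to be day cases in each arm, which the article does not describe, and in step 4 the inpatient difference changes sign.

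The protocol also confines these analyses to confidence intervals and hypothesis generation. This limits the consequence, but the reason given is low power. An interval centred on the wrong value is not mended by calling it imprecise.

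Nor should the spurious differences be read against the 2.5-unit IPSS margin as a threat to the trial's conclusion. That margin governs the overall 12-month comparison, and no equivalence claim within day-case or inpatient groups is planned.

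Finally, the item might mean a planned pathway, in which case the day-case part of the objection falls. The article does not say so, and length of stay cannot be read that way. Two further inferences also lack support: the Blinding section addresses only participants and their general practitioners, so it does not establish that staff aware of allocation decide discharge; and no passage says that a planned day-case listing was recorded.

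**Conclusion.** The point holds as a badly chosen modifier. Realised stay is a post-randomisation key secondary outcome that the protocol expects ThuVARP to change, so treatment contrasts within day-case and inpatient groups are liable to bias, and the interaction possibly so. Under the assumptions above, the within-group bias is about +0.3 to +2.2 IPSS units in day cases and +0.2 to +1.2 in inpatients. The interaction bias is about 0.1 to 1.0 units, with false positives of about 5 to 8%, when selection works alike in both arms; it becomes large only if selection differs by arm. Every input except the SD and the number per arm is assumed, so these figures show what is possible and do not predict the result. The primary equivalence analysis is unaffected. Severity is minor to moderate.

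**What to change.** Remove realised length of stay and realised day-case status from the effect-modifier list and analyse them only as outcomes. If a day-case question is wanted, define the modifier as planned day-case or inpatient status fixed before randomisation, where that was recorded. Where it was not, any analysis by realised stay should be labelled non-randomised and exploratory, with a statement that the groups may differ in prognosis between arms.

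Removing the item is a wording change in the analysis plan, with no effect on sample size or the primary analysis. Using planned status costs nothing more only if it was captured; the article does not show that it was, so this should be checked before it is promised.

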### Economic data analysis

The trial includes a formal economic evaluation comparing the costs and cost-effectiveness of the interventions from an NHS and broader societal perspective (with personal social service and patient costs reported separately). Only resources used in relation to the treatment of LUTS, or urinary retention secondary to BPO, will be analysed from randomisation at the time of surgery, to 12 months follow-up. The cost of the interventions and the use of primary and secondary NHS services by the men, personal and social service costs, costs to the men arising from their treatment (e.g. travel, over-the-counter medication) and productivity costs will be estimated through the collection of resource-use data as outlined earlier and the valuation of these data.

Micro-costing of the initial hospital stay will be needed and therefore Trust finance departments of the participating hospitals will be approached in order to value the initial NHS resources used. All other resource use will be valued using information from the laser company, routine sources and information from the patients themselves.

The EQ-5D-5L is administered at baseline and at 6 weeks, 3 and 12 months after the operation. These values will be transformed into utility scores [17] and individual QALYs will be calculated using the area under the curve approach.

Initially, regression techniques adjusting for pre-specified baseline characteristics, randomisation variables and a centre effect will be used to evaluate the difference in costs. Boot-strapped confidence intervals will be used, given the potential non-normality of the cost data. The same model will be used to evaluate the difference in QALYs. The differences in terms of the two primary outcomes will be evaluated according to the statistical analysis plan.

For the base case economic analysis, for the two perspectives, cost-effectiveness will be assessed using the Net Benefit framework over a range of values for the QALY.

A secondary economic analysis, for the two perspectives, will be conducted in which the outcomes will be the co-primary outcomes of the trial (i.e. IPSS and urine flow, Qmax). For this analysis the differences in costs and effects will be examined. If one arm is dominant (i.e. less costly and more effective) no further incremental analysis will be conducted. Otherwise an incremental cost-effectiveness ratio (ICER) will be calculated. Seemingly unrelated regressions (SUR) will be used, if appropriate, to account for the potential correlation between costs and the IPSS score/Qmax values.

Uncertainty will be addressed using cost-effectiveness acceptability curves and sensitivity analyses. One aspect of uncertainty is likely to be that of missing data. As with the main analysis, a pre-specified analysis plan will be created in which the plausible assumptions about missing data will be created and tested using these assumptions within the sensitivity analyses.

Additionally the costs of surgeon training for the ThuVARP laser technique will be estimated. This will be reported to allow policy makers to more accurately estimate the costs of service reconfiguration if the ThuVARP laser is shown to be equivalent to the TURP. These costs will also be incorporated in one of the sensitivity analyses.

No modelling has been specified within this evaluation, as the work is seen as a definitive trial, and experience has shown that most uncertainty in relation to cost differences will be captured within the first 12 months, the duration of this trial.

### Qualitative data analysis

A standardised approach will be employed to explore the interview data in accordance with published qualitative research methods. Face-to-face patient interviews will be conducted where possible, with telephone interviews included for other study sites, which will be carried out by an experienced qualitative researcher. Interviews will be digitally recorded, transcribed verbatim and uploaded into a qualitative software package to aid data management (QSR NVivo 10). Analyses will be conducted by the qualitative researcher according to the principles of thematic content analysis. Recordings will be listened to and transcripts read and re-read for familiarisation. Segments of text will be ‘coded’ by assigning descriptive labels. Codes will be grouped on the basis of shared properties to create themes, and coded transcripts will then be examined and compared to inductively refine and delineate themes (constant comparison). A subset of interviews will be independently analysed by a second study researcher and coding discrepancies discussed to maximise rigour and reliability. Plausibility of data interpretation will be further discussed between the study team, including the clinical co-applicants, throughout the analyses. Descriptive summary accounts of the interviews will be prepared.

Theoretical purposive (non-probability) sampling will be used, where explanations, developing to describe the data during analyses, guide further sampling and data collection. Maximum variation sampling will also ensure the diverse characteristics of the population are sampled (e.g. participants varying in age, clinical history and surgery received). Sampling and analyses will continue in iterative cycles until no new themes are emerging and established themes cease evolving: data saturation. It is anticipated that approximately 30–40 participants will be required, with up to 20 per procedure to allow for sampling of those with LUTS and urinary retention as the reason for their treatment.

## Discussion

This article describes a multicentre randomised trial to compare ThuVARP to the current gold standard TURP surgery for benign prostatic obstruction. The aim is to determine the relative clinical and cost effectiveness of the two alternative procedures, within the NHS.

The most significant challenge for the trial, during the recruitment phase, has been the capacity of participating Trusts to undertake the required surgery. Randomisation occurs in the operating theatre whilst the patient is under anaesthetic. Operating theatre availability and hospital bed pressures within Trusts, particularly during the winter months, slowed recruitment for this elective procedure, despite a ready pool of willing participants. Protected research operating time secured at two participating Trusts, the advent of day case procedures and multiple surgeons at sites, helped to overcome these challenges, albeit with additional time for recruitment required. It should be noted that the very difficulties experienced in conducting this trial, with the shortage of hospital beds impacting on the capacity for Trusts to operate, are the very same issues which ThuVARP has the promise to address, with its potential for shorter hospital stays, and shift to day case procedures.

This randomised study will provide the high-quality evidence, in an NHS setting with a range of patient-reported, clinical and cost-effectiveness outcomes, which will underpin and inform future NICE guidance in a timely manner.

### Trial status

The UNBLOCS trial began recruitment in June 2014, with the first participant enrolled on 23 July 2014. Recruitment completed on 31 December 2016.

## Abbreviations

BPO: Benign prostatic obstruction
BRTC: Bristol Randomised Trials Collaboration
CI: Chief Investigator
CONSORT: Consolidated Standards of Reporting Trials
CRF: Case report form
DMEC: Data Monitoring and Ethics Committee
EAU: European Association of Urology
EQ-5D-5L: EuroQol Group’s five-dimension health status questionnaire
FBC: Full blood count
GP: General practitioner
HES: Hospital Episode Statistics
HoLEP: Holmium Laser Enucleation of the Prostate
HTA: Health Technology Assessment
ICIQ-LUTSqol: International Consultation on Incontinence Questionnaire – Lower Urinary Tract Symptoms Quality of Life
ICIQ-MLUTS: International Consultation on Incontinence Questionnaire – Male Lower Urinary Tract Symptoms
ICIQ-MLUTSsex: International Consultation on Incontinence Questionnaire – sexual function associated with Male Lower Urinary Tract Symptoms
ICIQ-satisfaction: International Consultation on Incontinence Questionnaire – Satisfaction
IIEF: International Index of Erectile Function
IPSS: International Prostate Symptom Score
ISCP-WBA: Intercollegiate Surgical Curriculum Programme work-based assessments
ISRCTN: International Standard Randomised Controlled Trial Number
LUTS: Lower Urinary Tract Symptoms
NHS: National Health Service
NICE: National Institute for Health and Care Excellence
NIHR: National Institute for Health Research
NRES: National Research Ethics Service
PI: Principal Investigator
PIS: Patient Information Sheet
PRO: Patient-reported outcome
PSA: Prostate-specific antigen
PSS: Personal Social Services
PVR: Post-void residual
QALY: Quality-adjusted life years
Qmax: Maximum urine flow rate
RCT: Randomised controlled trial
RUL: Resource Use Log
SD: Standard deviation
ThuVARP: Thulium laser transurethral vaporesection of the prostate
TURP: Transurethral resection of the prostate
U&Es: Urea and electrolytes
UK: United Kingdom
UNBLOCS: UriNary oBstruction relieved by Laser Or Conventional Surgery
VV: Voided volume
